**S2 Protocol. Protocol (in English).**

Clinical study protocol

Clinical study title: Comparison of the effects of oral hygiene instruction and periodontal treatment in patients with type 2 diabetes mellitus
（Comparison of the effects of oral hygiene instruction and periodontal treatment on patients with type 2 diabetes mellitus）

Principal investigator: [name]

Department of Preventive Dentistry, Okayama University Graduate School of Medicine, Dentistry and Pharmaceutical Sciences, Okayama, Japan

[name]

Telephone no. (ext.): [contact] [name]

[contact]

E-mail: [contact]

Emergency contact (medical office number): [contact]

Planned duration of study: March 1, 2014 – March 31, 2016.

Comparison of the effects of oral hygiene instruction and periodontal treatment in

patients with type 2 diabetes mellitus

Study protocol

1. Background

The “Basic Matters Related to Dental and Oral Health Promotion” are based on the “Dental and Oral Health Promotion Law” enacted in August 2012. It describes the relationship between oral status and general health, between dental diseases and lifestyle habits, and between oral health and medical expenses, as well as the promotion of research on prevention and treatment methods that are effective from their relation to dentistry. Innovation is needed especially in dental-medical collaborative model projects for diabetes patients, as the close relationship between periodontal disease and diabetes continues to be elucidated.

2. Study objectives and necessity

In this study, type 2 diabetes patients being treated on an outpatient basis at Okayama University Hospital will be divided into two groups, an oral hygiene health instruction group (given guidance on plaque control only) and a non-surgical periodontal treatment group (given guidance on plaque control and periodontal treatment). The purpose of this study is to compare the results of tests (clinical and blood biochemistry tests) performed 6 months after the conclusion of periodontal treatment (including full mouth scaling and root planing), and the effects on changes in quality of life (QOL) in these two groups.

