Some of the above examinations will be performed a total of three times: at the start of the study, after 3 months, and after 6 months. Periodontal treatment will be completed by 2 months from the start of the study. Oral hygiene instruction will be provided to both groups at the start of the study, after 3 months, and after 6 months. In cases where there is a change in diabetes treatment during the study period, the details will be recorded.

(3) Planned duration of subject participation

Six months.

(4) Usage, dosage and administration period of study drugs

Not applicable.

(5) Study drug dosage form/content, properties, packaging, labeling, and storage

Not applicable.

(6) Provisions regarding concomitant medication (therapy)

Not applicable.

(7) Drug withdrawal method

Not applicable.

(8) Management and delivery procedures for study drugs

Not applicable.

(9) Drug administration guidance information

Not applicable.

(10) Case enrollment, allocation

Subject enrollment:

The principal investigator or a co-investigator will: 1) obtain written consent; 2) write the date on which consent was obtained and the items needed to link the subjects to the subject identification code on the subject identification code list kept by the principal investigator; 3) submit the case report form using the subject identification code to the study office (medical office for the Department of Preventive Dentistry); and 4) report immediately in the event of consent withdrawal, discontinuation, or dropout.

Subject allocation:

The subjects will be allocated to the treatment groups with a table of random numbers. Using a stratified block randomization allocation method, adjustments will be made according to baseline serum HbA1c (≥8% and <8%), whether a patient is receiving insulin treatment, and types and number of drugs (≤2 or ≥3) a patient is taking.

(11) Handling at completion of study

After the completion of the study, the principal investigator will provide the treatment he considers to be the most appropriate for each subject, including treatment based on the findings obtained in this study.

7. Assessments

(1) Primary endpoint

Serum HbA1c (National Glycohemoglobin Standardization Program [NGSP] value)

(2) Secondary endpoints

Periodontal status (number of teeth present, probing pocket depth, clinical attachment level, bleeding on probing, Plaque Control Record)

Hematological index (glycated albumin)

Blood biochemical index (oxidative stress balance)

QOL

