  3. Continuation in the study is difficult due to exacerbation of complications.
  4. A subject is discovered to be pregnant.
  5. The entire study is discontinued.
  6. Dental treatment is found to be necessary for a subject in the oral hygiene instruction group after assignment.
  7. A physician determines that discontinuation is advisable for some other reason.

10. Handling when an adverse event occurs

(1) Response to patients when an adverse event occurs

When an adverse event that requires treatment occurs in a subject, the subject will be notified and appropriate medical care for the adverse event will be provided.

(2) Report of a serious adverse event

If a serious adverse event occurs or there is concern of such an event occurring, a report will be made immediately to the Hospital Director of Okayama University Hospital.

11. Report of deviation from protocol

The following matters are provided in accordance with GCP:

- The principal investigator and co-investigators will not deviate from or make changes to the study protocol before obtaining approval from the Hospital Director based on advance review of the Ethics Committee.
- The principal investigator and co-investigators may deviate from or change the study protocol before obtaining advance approval from the Ethics Committee for compelling reasons in order to avoid an emergency. In such cases, the principal investigator or a co-investigator will submit the details regarding the deviation or change and the associated reasons, together with a proposal for revision of the study protocol if necessary, to the Ethics Committee without delay, and approval from the Ethics Committee and Hospital Director will be obtained.
- In cases of deviation from the study protocol, the principal investigator or a co-investigator will record all items of deviation and the reasons for them.

12. Completion, discontinuation, or cessation of study

(1) Study completion

At the completion of the study, the principal investigator will submit a study completion report to the Hospital Director without delay.

(2) Study discontinuation or cessation

The principal investigator will consider whether or not to continue the study in the event of either of the following:

1) Recruiting subjects is difficult and reaching the planned number of subjects is judged to be unlikely.

2) The Ethics Committee asks for changes to be made in the protocol or other matters, and those changes are judged to be difficult to make.

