When a decision is made to discontinue or cease the study, a report to that effect together with the reason will be made in writing to the Hospital Director without delay.

13. Study period

From March 1, 2014 to March 31, 2016.

14. Data aggregation and statistical analysis

Data analysis will be conducted from the following observations:

1) Role of plaque control instruction in type 2 diabetes patients: The significance of plaque control instruction will be investigated from a comparison between the start of the study and the time of reassessment in the oral hygiene instruction group, including its effect on QOL.

2) Significance of periodontal treatment: The effects of periodontal treatment in type 2 diabetes patients will be discerned from a comparison of the oral hygiene instruction group and the non-surgical periodontal treatment group.

15. Target patient number and rationale

The target patient number is 20 for each group (40 patients total).

The number of patients is calculated to be 20 based on analysis of the serum HbA1c level in a previous study (see reference) on periodontal treatment in diabetes patients. To determine the sample size when the *t*-test is used, calculations were performed using SPSS Samplepower (IBM, Tokyo, Japan). Under the conditions of α=0.05 and β=0.20, with a two-tailed *t*-test, the predicted HbA1c level was 7.31% in the oral hygiene instruction group and 6.51% in the non-surgical periodontal treatment group. With an assumed standard deviation of 0.8, significance was hypothesized when the mean serum HbA1c differed by 0.8% as a result of periodontal treatment. As a result, 17 patients are needed for the study. Assuming a 15% dropout rate, the number is set at 20 patients.

16. Subjects’ rights, safety, and disadvantage

(1) Human rights (protection of privacy)

Subject data are coded and test results are provided to the person conducting the analysis at Okayama University so that individual subjects cannot be identified. To combine the data from the examination table, questionnaire, and each test, the same symbols are given to the same subject being examined. After the study has been completed, these data will be destroyed.

(2) Patient safety, disadvantage

Health insurance and other measures needed to compensate for health damage to subjects are not adopted.

Reason: There is the possibility only of slight pain when blood is taken. No damage to health is foreseen.

17. Cost to patients

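### Section 14 item 1 attributes an effect to plaque-control instruction from a before-after change in one arm, which this design cannot separate from other causes of change

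*Protocol*

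**What the plan says.** Section 14 of the protocol lists two lines of analysis. Item 1 concerns the role of plaque-control instruction: "The significance of plaque control instruction will be investigated from a comparison between the start of the study and the time of reassessment", carried out "in the oral hygiene instruction group, including its effect on QOL". Item 2 concerns periodontal treatment, whose effects "will be discerned from a comparison of the oral hygiene instruction group and the non-surgical periodontal treatment group".

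Section 2 defines the two arms, the second receiving its treatment in addition to the guidance: "an oral hygiene health instruction group (given guidance on plaque control only) and a non-surgical periodontal treatment group (given guidance on plaque control and periodontal" (the quote is cut before its last word). Section 6(2) confirms that instruction is common to both: "Oral hygiene instruction will be provided to both groups at the start of the study, after 3 months, and after 6 months".

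Two other provisions bear on a before-after change in the instruction arm. On diabetes care, section 6(2) says: "In cases where there is a change in diabetes treatment during the study period, the details will be recorded". Section 9 lists as a reason for discontinuation: "Dental treatment is found to be necessary for a subject in the oral hygiene instruction group after assignment".

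**The concern.** Item 1 speaks of a role, a significance and an effect on QOL, which are statements about what instruction does. Its evidence is one arm before and after. Every randomised patient receives instruction, so nothing in the trial shows what would have happened without it.

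If item 1 is followed as written, a change in the instruction arm can be reported as due to instruction when it arose from something else. What is at stake is a secondary conclusion on instruction, with QOL named explicitly. An analysis plan could choose the test, the covariates or the time point, but it could not create a group without instruction. The fault therefore lies in what the protocol itself fixes.

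**Working it through.** **1. The plan's own figure.** Section 15 gives a two-sided t-test "Under the conditions of α=0.05 and β=0.20", means of 7.31% and 6.51%, SD 0.8, 17 patients, and 20 after 15% dropout. The standardised difference is (7.31 − 6.51)/0.8 = 1.0. By the noncentral t distribution, power is 0.781 with 16 per group and 0.807 with 17 per group, so 17 is right. Then 17/0.85 = 20. The figure reproduces, but it covers only the between-group comparison of item 2. No calculation supports item 1.

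**2. What each comparison identifies.** Let B be the mean change that would occur without instruction, I the effect of instruction, and P the effect of periodontal treatment added to instruction.

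- Instruction arm, mean change: B + I
- Treatment arm, mean change: B + I + P
- Difference between arms: P

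The randomised difference gives P, and I cancels. The before-after change in the instruction arm gives only the sum B + I. Nothing in the trial gives B, so I cannot be recovered.

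**3. What can enter B, or distort the sum.**

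- Time trend and the consequences of taking part, with repeated examinations over six months.
- Regression to the mean. The entry criteria in section 4 set no HbA1c or QOL threshold, so this may be small, but the design cannot rule it out.
- Changes in diabetes treatment, which section 6(2) records if they occur.
- Selective loss. Section 9 criterion 6 applies only to the instruction arm. If patients who leave under it have no later measurement, the before-after comparison rests on a selected remainder.

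**4. Illustration of size.** Item 1 names neither HbA1c nor a test, so this step is hypothetical. From the protocol: n = 17, SD 0.8, two-sided α = 0.05. Assumed, because the protocol gives no figure: pre-post correlation r of 0.5 to 0.8 and a background fall d of 0.1 to 0.4 percentage points. The instruction effect I is set to zero.

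SD of change = 0.8 × √(2(1 − r)), which is 0.800, 0.620 and 0.506 for r = 0.5, 0.7 and 0.8. Noncentrality = d × √17 / SD of change, on 16 degrees of freedom. For d = 0.3 and r = 0.7 this is 0.3 × 4.123/0.620 = 2.0, and the probability of a significant paired t-test is 46.7%.

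| Background fall d | r = 0.5 | r = 0.7 | r = 0.8 |
|---|---|---|---|
| 0 | 5.0% | 5.0% | 5.0% |
| 0.1 | 7.7% | 9.6% | 12.0% |
| 0.2 | 16.3% | 24.0% | 33.5% |
| 0.3 | 30.7% | 46.7% | 63.2% |
| 0.4 | 49.1% | 70.5% | 86.4% |

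With all 20 patients, the ranges over r are 8% to 13%, 19% to 39%, 36% to 71% and 57% to 92% for falls of 0.1, 0.2, 0.3 and 0.4. More patients make a false attribution more likely, because the problem is bias and not imprecision.

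**The case against.** The strongest reply is that item 1 is a side analysis. Section 2 states the purpose as a comparison of the two groups, and the sample size rests on that comparison alone. Item 1 names no test, no α and no decision rule. The word significance may mean importance, as it appears to in the heading of item 2. Reporting within-arm change is ordinary practice, and a paired test labelled exploratory would be acceptable. The background falls used above have no source in the protocol, and at 0.1 points the excess over 5% is small.

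Much of this stands. It limits the reach of the point and makes the percentages illustrative only. It does not rescue the causal wording: a role and an effect on QOL are claimed whether or not a p-value is computed, and the step from B + I to I is unsupported either way.

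A reader might infer more than the protocol supports, in four ways:

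- That item 1 puts the case for insurance coverage at risk. Section 2 ties that aim to periodontal treatment, which item 2 judges by the randomised comparison.
- That the plan leads to claiming a treatment effect because one arm changes significantly and the other does not. Section 14 plans no before-after comparison in the treatment arm.
- That changes in diabetes drugs are expected. The text is conditional and only provides for recording them.
- That the main comparison is compromised. The lack of an instruction-free group does not touch it, because instruction is common to both arms and cancels.

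**Conclusion.** The point holds in limited form. The protocol draws a conclusion about the effect of plaque-control instruction, including on QOL, from a comparison that cannot isolate that effect. This follows from the arm definitions alone and needs no numerical assumption.

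How often a false attribution would arise cannot be determined from the protocol. Under the stated assumptions it runs from 8% to 12% of trials for a background HbA1c fall of 0.1 points to 49% to 86% for a fall of 0.4, and it is 5% if there is no background change. No corresponding figure can be given for QOL, because the protocol gives no variability for it. The consequence is confined to a secondary conclusion.

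**What to change.** Restate item 1 as a descriptive or exploratory summary of change within the instruction arm: mean change with 95% confidence interval, QOL included, and no statement that instruction caused the change. If a paired test is kept, label it exploratory. Report alongside it how many patients had a change in diabetes treatment and how many were discontinued under section 9 criterion 6.

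Add one sentence to section 14 saying that conclusions on effect come only from the between-group comparison in item 2, which estimates periodontal treatment added to instruction.

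The cost is a few sentences, with no change to sample size, visits or data collection. The downside is that the sponsor gives up a secondary claim for instruction. Supporting that claim would need a concurrent group without instruction, which is a different design.

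### The only between-group test named is an unadjusted t-test on HbA1c levels; the protocol should commit to adjusting for baseline HbA1c and the stratification factors

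*Protocol*

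**What the plan says.** Section 7(1) gives the primary endpoint as serum HbA1c and does not say whether the level, the change or an adjusted value is meant. Under section 6(2), examinations take place at the start, at 3 months and at 6 months, and HbA1c is among the blood tests.

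Section 6(10) describes stratified block randomisation in which "adjustments will be made according to baseline serum HbA1c (≥8% and <8%), whether a patient is receiving insulin treatment", together with the types and number of drugs (≤2 or ≥3).

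On the between-group analysis, section 14, item 2, says: "The effects of periodontal treatment in type 2 diabetes patients will be discerned from a comparison of the oral hygiene instruction group" and the treated group. It names no test, model, covariate or time point.

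The t-test appears in section 15: "To determine the sample size when the *t*-test is used, calculations were performed using SPSS Samplepower". The inputs there are "Under the conditions of α=0.05 and β=0.20", two-tailed, and "the predicted HbA1c level was 7.31% in the oral hygiene instruction group and 6.51% in the non-surgical periodontal treatment group". The section continues: "With an assumed standard deviation of 0.8, significance was hypothesized when the mean serum HbA1c differed by 0.8% as a result of periodontal treatment". These are HbA1c levels, and baseline does not enter the calculation.

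**The concern.** A patient's HbA1c at entry usually predicts HbA1c six months later. The protocol treats baseline HbA1c as important enough to stratify on, but the only between-group test it names makes no use of it.

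Two things follow if that test becomes the analysis. First, the variation between patients that baseline could explain stays in the error term, so the confidence interval is wider than it need be. Second, stratified allocation makes the groups more alike than simple randomisation would, while the ordinary t-test computes its standard error as if they were not. The standard error is then too large and the test rejects less often than its nominal 5%.

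This matters because the trial is small and sized for a difference of a full standard deviation. Section 2 hopes to use the result as evidence for insurance coverage of periodontal treatment. A smaller true effect would have less chance of being shown than the collected data allow.

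**Working it through.** **Inputs from the protocol.** Difference 7.31 − 6.51 = 0.80; SD 0.8; α = 0.05 two-sided; power 0.80; dropout 15%; 20 per group (section 15). Stratification factors as in section 6(10).

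**Inputs assumed.** The baseline-to-follow-up correlation r is not given, so it is shown from 0.3 to 0.8. Block size and stratum frequencies are not given either. Data are taken as normal.

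**Step 1: the plan's own figure.** The standardised effect is 0.8/0.8 = 1.0. With the noncentral t distribution, power is 0.781 at 16 per group and 0.807 at 17 per group, so 17 per group are needed. Then 17/0.85 = 20. Both figures reproduce. The 17 in "As a result, 17 patients are needed for the study" is therefore a per-group number.

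**Step 2: precision of the unadjusted test.** With 17 completers per group and an observed SD of 0.8, the 95% CI half-width is t(0.975; 32) × 0.8 × √(2/17) = 2.037 × 0.8 × 0.343 = 0.56.

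**Step 3: effect of baseline adjustment.** The residual SD is 0.8 × √(1 − r²), the variance removed is r², and the degrees of freedom are 2n − 3. At 17 per group the half-width is 2.04 × residual SD × 0.343.

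| r | Variance removed | Residual SD | CI half-width | n per group for 80% power at 0.8 | Power at 0.8 with 17 per group |
|---|---|---|---|---|---|
| unadjusted | – | 0.80 | 0.56 | 17 | 0.81 |
| 0.3 | 9% | 0.76 | 0.53 | 16 | 0.84 |
| 0.5 | 25% | 0.69 | 0.48 | 13 | 0.90 |
| 0.6 | 36% | 0.64 | 0.45 | 12 | 0.94 |
| 0.7 | 49% | 0.57 | 0.40 | 10 | 0.98 |
| 0.8 | 64% | 0.48 | 0.34 | 7 | 0.997 |

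**Step 4: power at smaller true differences.** This was simulated with 40 patients, three stratification factors, assumed blocks of 4, 15% dropout, and ANCOVA with all three covariates.

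| r | True difference | t-test | ANCOVA |
|---|---|---|---|
| 0.5 | 0.5 | 42% | 52% |
| 0.5 | 0.6 | 57% | 67% |
| 0.7 | 0.5 | 42% | 67% |
| 0.7 | 0.6 | 56% | 83% |
| 0.8 | 0.5 | 41% | 82% |
| 0.8 | 0.6 | 56% | 92% |

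At r = 0.3 the gain is only about 2 points.

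**Step 5: type I error after stratified blocks.** With HbA1c as the only stratification factor and blocks of 4 (8,000 runs per setting), the unadjusted t-test rejects a true null hypothesis in about 5% of runs at r = 0, 3.2% to 3.4% at r = 0.5, 2.0% to 2.6% at r = 0.7 and 1.3% to 2.2% at r = 0.8. With three factors the rates are 4.5%, 2.9% and 2.6% at r = 0.5, 0.7 and 0.8. A further three-factor run at r = 0.7 gave 3.6%. The direction is the same throughout, while the size depends on the assumed strata. ANCOVA gave 4.5% to 5.3% in the first setting and 4.7% to 5.1% in the second.

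**The case against.** The strongest objection is that the protocol does not prescribe the t-test as its analysis. A reader might infer that it does, because no other between-group test is named. But section 14 fixes no method, and section 15 uses the t-test to find a sample size. Sizing without adjustment is the cautious choice when the correlation is unknown, and it is compatible with an adjusted analysis. A statistical analysis plan that is not shown may specify one. This stands, and the point is therefore conditional. It remains worth making because the protocol stratifies on a prognostic baseline value and the only test it names ignores that value.

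A reader might also infer that half the information is wasted. That needs r near 0.7, which the documents do not supply. If change from baseline were analysed, the gain would be smaller. With equal variances at both times, the variance ratio of ANCOVA to the change score is (1 − r²)/(2(1 − r)) = (1 + r)/2, a reduction of 25% at r = 0.5, 15% at 0.7 and 10% at 0.8.

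Nor does it follow that a true effect below 0.56 would be missed. That figure is a threshold for the observed difference at an SD of exactly 0.8. The t-test still has about 42% power at a true difference of 0.5 and 56% at 0.6.

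Finally, one simulation (6,000 runs, Monte Carlo error about 0.3 points) put ANCOVA at 5.7%, slightly above nominal. The other settings gave 4.5% to 5.3%, so this does not outweigh the gain.

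**Conclusion.** The concern holds as a recommendation on efficiency. If the groups are compared with the only test named, the analysis gives up between 9% and 64% of variance reduction over r = 0.3 to 0.8. Its true type I error is also below 5%, roughly 2% to 4.5% for r = 0.5 to 0.8, with 1.3% in the most extreme setting tried. The loss is negligible at low r and considerable at r = 0.7 or more.

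The consequence is a wider interval and a conservative test. Randomisation still protects against bias, stratification already limits imbalance in baseline HbA1c, and the type I error is not inflated. The sample size is correct on its stated inputs, and the unadjusted test has its planned power of about 81% at a difference of 0.8.

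The sizes rest on the assumed correlation, block size, stratum frequencies and normality. The direction requires only that baseline and follow-up HbA1c are positively correlated.

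**What to change.** In section 14, item 2, state that the primary analysis is an ANCOVA of 6-month HbA1c on treatment group, with continuous baseline HbA1c, insulin use (yes/no) and number of drugs (≤2/≥3) as covariates. Report the adjusted mean difference with its 95% confidence interval. Keep the unadjusted t-test as a sensitivity analysis and leave the target at 20 per group.

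The cost is one or two sentences. Every covariate is already collected for allocation, and no visit, test or patient is added. Fixing the model in advance also closes the choice between level, change and adjusted value that sections 7(1) and 14 leave open.
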